### Recruitment and Screening

For this trial, we are focused on recruiting geographically, racially, and ethnically diverse informal caregivers to ensure generalizability. We have established partnerships with a variety of organizations dedicated to supporting caregivers and care recipients (eg, National Alliance of Caregiving and Boston Ministerial Alliance) that share our recruitment materials (eg, flyer) on social media and listservs. Additionally, we directly contact caregivers from our previous nonclinical trial studies that indicated interest in learning about additional research opportunities. Interested caregivers use a link or QR code on flyers, social media ads, and email blasts to fill out a web-based eligibility questionnaire through REDCap (Research Electronic Data Capture; Vanderbilt University) [48]. Caregivers who want more information on the study can contact the research assistant (RA) before completing the screening in REDCap. Ineligible caregivers receive an on-screen message at the end of the screening in REDCap notifying them of their ineligibility along with a link to a resource sheet. For participants who meet initial eligibility criteria, a final survey page appears where they confirm their interest in participating and provide suitable times for a 20- to 30-minute enrollment phone call. During this call, the RA administers the Short Portable Mental Status Questionnaire (SPMSQ; for those over the age of 65 years) [47] and the Functional Assessment Staging Tool (FAST) [46] to finalize eligibility criteria.

### Ensuring Validity of Participant Data by Avoiding “Imposter” Participants

Previous research has shown that remote studies have an increased risk of enrolling “imposter” participants (ie, participants who misrepresent themselves to appear eligible for a study) [49,50]. In a web-based study using MTurk (a crowdsourcing service), Hydock [49] found that more than 12% of participants falsified their identities “for the chance of financial gain.” To address this concern, our team has identified “red flags” that suggest that a participant is misrepresenting their identity and requires additional attention and screening, including (1) large volumes of back-to-back inquiries following a similar format (eg, all emails are firstnamelastname ####@gmail.com), (2) spelling mistakes and grammatical errors, (3) incorrect or inconsistent survey responses (eg, one participant wrote they heard about this study on Craigslist), (4) providing out-of-service or Google Voice (Google LLC) numbers (the use of Google Voice numbers has been cited as a commonality among many imposter participants [51]), (5) poor sound quality during phone calls, and (6) exaggerated or illogical statements during phone calls (eg, stating, “I take my father with advanced dementia to the gym and we work out together”). These are not exclusion criteria but rather indicate to the research team that it is possible that the inquiry about the study was made by a potential imposter participant.

Our team has developed a protocol to prevent imposter participants from enrolling. First, when participants inquire about the study on public-facing platforms (eg, “Rally,” a web-based platform for advertising research studies across our hospital system), we call them before sending the link to the screening survey. This has been cited in other studies as a strategy to eliminate imposter participants [51]. Second, we have used a “three-strike” system. Once a potential participant has displayed 3 red flags (described above), they are no longer considered eligible for this study. We move these participants to the “suspected imposter” section of our log and do not continue contact attempts; we have noticed that the more we engage with potential imposter participants, the more false inquiries we receive. Third, we do not provide compensation for the completion of baseline assessments; instead, our compensation is divided up between posttest and follow-up, which discourages imposter participants who might enroll for the baseline compensation and then drop out. So far, we have identified 44 suspected imposter participants (approximately 36%) out of the 123 inquiries we have received. We acknowledge that these procedures have the potential to exclude eligible participants (ie, false negatives); however, as a team, we agreed to prioritize the integrity of the data for this small-scale feasibility RCT.

### Enrollment

If participants are deemed eligible during the enrollment call, the RA reviews the consent form, answers any questions, and assists the participant with signing the consent form by electronic consent on REDCap. Once the consent form has been signed, the RA emails baseline surveys to the participant through REDCap. Study staff randomize the participants after baseline completion. Our senior biostatistician programmed randomization into REDCap and stratified by gender (given that caregivers tend to be women) [1]. The RA emails the participant instructions to download and login to their assigned app (HMP or WA). To protect participant confidentiality, the study team creates accounts with study-specific login email addresses (eg, [contact] and [contact]) so there are no personal identifiers (eg, email, name, and date of birth) associated with participants’ accounts. The spreadsheet containing login information and the corresponding participant’s information is stored in a secure, password-protected database. After receiving instructions and login information, participants have the option of scheduling a phone call or Zoom (Zoom Video Communications) meeting with the RA to assist with setting up their app. Figure 2 summarizes the recruitment and enrollment procedures.

**Figure 2 figure2:**
[figure not shown]
Recruitment and enrollment procedures. FAST: Functional Assessment Staging Tool; HMP: Healthy Minds Program; SPMSQ: Short Portable Mental Status Questionnaire; WA: Wellness App.

### Treatment Conditions

Participants in both treatment conditions (HMP or WA) listen to prescribed guided listening on a mobile app for at least ten minutes per day (70 minutes per week) for 12 weeks. Participants download their assigned app through the Google Play (Google LLC) or Apple App (Apple Inc) Store, and participants are blinded to the condition (ie, intervention or control). Participants can complete their daily listening at any time of day. Both apps suggest a specific ordering of the audio clips, but participants can choose to listen to any audio content within the app based on their preferences—the only requirement is that they listen for at least 10 minutes per day. Participants are encouraged to turn on “push notifications” to remind them to do their daily listening, but this is not mandatory. Both apps allow participants to view their daily listening history and mark which content has already been listened to.

### Healthy Minds Program

Full details on the HMP app can be found on the web at Healthy Minds Innovations [52]. In summary, HMP is a self-guided meditation app that includes training in mindfulness through the 4 “pillars” of mental training: awareness, insight, connection, and purpose. Guided listening in each pillar trains listeners to be more focused and self-aware in the present moment (awareness), develop skills to strengthen compassionate connection with others (connection), learn about how a person’s thoughts affect their emotions (insight), and stay more grounded in one’s values and principles (purpose) [41,52]. Each pillar contains guided listening consisting of brief lessons labeled “learn” and meditations labeled “practice.” Participants are asked to complete at least 10 minutes of “practice” each day (meditations can be set for 5, 10, 15, 20, or 30 minutes) and are encouraged to listen to the “learn” content in conjunction with their practices. Participants have the choice to make any meditation “sitting” or “active” and can also select the speaker of each meditation, allowing for racial, ethnic, and gender diversity of the speaker. Our multidisciplinary team tailored the HMP app text that introduces and describes the mindfulness exercises to include language, case-based scenarios, and stressors that are common among caregivers of persons with ADRD (eg, gratitude for positive aspects of caregiving).

### Wellness App

WA is an investigator-developed time- and dose-matched control that offers daily caregiver-related guided listening consisting of knowledge-based podcasts for the 12-week intervention. If podcasts are longer than 10 minutes, caregivers are instructed to spread the listening out over multiple days to ensure that they are only listening for 10 minutes per day. All podcasts were individually selected by the study team to ensure that their content was relevant for caregivers of persons with ADRD. Examples of topics include “money and the unique needs of the older caregiver” and “how dementia affects sleep cycles.” Study staff also listened to ensure that no skills related to mindfulness or meditation were taught in any podcast to remove potential confounds. On the basis of feedback from 13 WA participants, we reviewed participant ratings of podcast quality and updated content to best meet the needs of participants in the control. For example, we replaced “overly negative” or “boring” content with more uplifting stories or engaging podcasts. The app has successfully been used as a control in multiple previous studies testing app-based meditation interventions [53,54].

### Strategies for Adherence

Regardless of group, participants are sent a text message each Monday of the intervention reminding them to listen to their daily content for at least ten minutes per day (ie, 70 minutes per week). This text message also includes a brief weekly survey with process measures (Textbox 1). Study staff members download and review participants’ listening data each Thursday. If a participant does not listen to at least 75% of their recommended listening in the past week (ie, <52.5 total minutes), a study staff member texts the participant a visual (ie, a “meme”) reminder catered toward their treatment condition (Multimedia Appendix 1). If participants do not consent to “meme” reminders, they receive a text message catered to their treatment condition instead (Multimedia Appendix 2). Participants who do not consent to receive text messages receive all reminders and surveys through email. If a participant does not listen to at least 75% of their recommended listening for 2 consecutive weeks, a study staff member calls this participant to troubleshoot potential barriers to adherence. Participants are also offered a monetary incentive for participating in the study (ie, US $20 for completing their posttest assessment and US $30 for completing their follow-up assessment, for a total of US $50).

Secondary outcomes.
**Demographics (pretest)**
Age; gender; biological sex; sexual orientation; race; ethnicity; educational level; employment status; occupation; income; marital status; housing situation; languages spoken; health insurance status; zip code; importance of religion or faith; mental health history; current psychotropic and pain medication intake; overall physical health status; number of individuals to provide informal caregiving to; patient’s diagnoses; relationship to patient; duration of caregiving; number of hours of caregiving per week; and whether caregiver is living with patient
**Outcome measures (pretest, posttest, and follow-up)**
Perceived Stress Scale-10 [55,56]: assesses perceived stress using a 5-point Likert scaleHospital Anxiety and Depression Scale [57]: 14-item measure to assess symptoms of emotional distress (anxiety and depression)Patient-Reported Outcomes Measurement Information Systems (PROMIS) Sleep Disturbance Short Form [58]: 8 items assessing sleepApplied Mindfulness Process Scale [59]: assesses mindfulness in 3 domains: decentering, positive emotion regulation, and negative emotion regulationCaregiver Reaction Scale [60]: assesses caregiver burden. We are administering the following subscales: role entrapment (4 items); role overload (4 items); mastery as a caregiver (4 items); self-mastery (4 items); workplace productivity (5 items)Healthy Minds Index [61]: a 17-item measure based on the Healthy Minds Program framework that assesses awareness, connection, insight, and purpose
**Process measures (weekly)**
Emotional Distress Thermometer: scale (0-10) to assess how caregivers rate their level of distress each week: “During the past week, how would you rate your emotional distress on a scale from 0 to 10? (0=not at all; 10=extremely emotionally distressed)”Sleep Thermometer: scale (0-10) to assess how caregivers rate their quality of sleep: “During the past week, how would you rate your quality of sleep on a scale from 0 to 10? (0=extremely low quality; 10=extremely high quality)”Mindfulness Thermometer: scale (0-10) to assess how caregivers rate their level of mindfulness each week: “During the past week, how would you rate your mindfulness on a scale from 0 to 10? (0=not at all; 10=extremely mindful)”Stress Thermometer: scale (0-10) to assess how caregivers rate their level of stress each week: “During the past week, how would you rate your stress on a scale from 0 to 10? (0=not at all; 10=extremely stressed)”
**Other measures (post)**
Modified Patient Global Impression of Change [62]: a 1-item questionnaire to assess the extent to which caregivers perceive the intervention’s improved functioning and symptoms: “Do you think your ability to manage stress associated with caring for your loved one with dementia is now improved, about the same, or worse, as compared to before your participation in this program?”Perceptions of daily meditations and podcast: we will assess caregivers’ perceptions of their app prescription by asking, “Do you think that the amount of prescribed app content was: too little, just enough, too much?”Perceptions of emails and text reminders: we will assess caregivers’ perceptions of email and text message reminders by asking, “Do you think that the amount of emails/texts you received was: too little, just enough, too much?”Perceptions of the overall study: we will assess caregivers’ perceptions of the study by asking, “Do you have any feedback about your experience in this program (content of the program, content of the text message reminders, etc) that you would like to share?”Perceptions of prompts and contacts in low adherence situations: We will assess caregivers’ perceptions of the number of prompts and contact in situations where they were not adhering to their practice by asking, “Do you think that the amount of prompts you received when you struggled with your practice was: too little, just enough, too much?”

### Feasibility Markers

Table 2 outlines the a priori set benchmarks and criteria that are consistent with guidelines for early feasibility studies [63]. We will assess the feasibility (acceptability and demand markers) of both mobile app treatment conditions and participants’ perceptions of their involvement in the study.

**Table 2 table2:** Primary outcomes.

Benchmarks and markers			Description		Criteria
**Acceptability benchmarks**					
	Feasibility of recruitment	We will assess the number of caregivers enrolled from the number of caregivers who were eligible		80 caregivers will be recruited in 6 months; ≥70% of eligible caregivers will enroll	
	Treatment satisfaction	We will use the Client Satisfaction Questionnaire [64] to assess caregivers’ satisfaction with the intervention		At least 70% of caregivers will have scores on the Client Satisfaction Scale over and above the midpoint in both the HMP^a^ and WA^b^ groups	
	Credibility and expectancy	We will use the Credibility and Expectancy Questionnaire [65] to assess caregivers’ perceptions that the treatment will work after learning about the study.		At least 70% of caregivers will have scores on the Credibility and Expectancy Scale above the midpoint in both the HMP and WA groups.	
**Demand benchmarks**					
	Adherence to treatment	We will assess data from the HMP app and the WA to measure adherence to the intervention and the control conditions		≥70% of caregivers will complete ≥75% of weekly prescribed minutes	
	Dropout	We will assess the number of caregivers who complete the study from the number of caregivers who started the study		>70% of caregivers who start the study will complete posttest assessments; ≤30% attrition	
**Data collection benchmarks**					
	Feasibility of weekly REDCap^c^ measures	We will assess the feasibility of the weekly REDCap measures sent to patients		≥70% caregivers will answer ≥75% of weekly REDCap measures	
	Feasibility of quantitative measures	We will assess the feasibility of the quantitative measures sent to caregivers at baseline, postintervention, and follow-up		No questionnaires fully missing in ≥25% caregivers	

^a^HMP: Healthy Minds Program.

^b^WA: Wellness App.

^c^REDCap: Research Electronic Data Capture

### Quantitative Assessments

The self-report measures and assessment domains were selected consistent with the purpose of the study [66]. Demographics are measured pretest, outcome measures are given during the main assessment points (pretest, posttest, and follow-up), and process measures are administered weekly. Textbox 1 provides a brief description of all self-reported assessments.

### Data Analysis

We will assess the acceptability and demand of the intervention in line with Bowen and colleagues’ standards for feasibility studies and components of the Behavioral Change Consortium’s Treatment Fidelity model [63,67]. Specifically, we will assess the acceptability, credibility, satisfaction, and perceived appropriateness and usefulness of the daily prescribed app content. Benchmarks and measurements for each feasibility construct are listed in Table 2. One-sided 95% CI will be calculated for each proportion to evaluate feasibility benchmarks. Depending on the nature of the estimate or comparison, exact binomial tests, Fisher exact tests, 2-tailed *t* tests, or correlations may be used to summarize the data and test for statistical significance. HMP and WA user data (ie, what content users listened to, when, and for how long) are collected automatically from users.

Consistent with guidelines for early feasibility studies, our analysis will not assess efficacy, as we are not powered to do so [68]. However, we will estimate between-group differences in changes from baseline to posttest (12 weeks) to follow-up (20 weeks) as proof of concept that the intervention shows promise with the intended population [63]. Variance components and effect sizes will be estimated for each outcome. We will use variance estimates from repeated-measures analysis of data on Perceived Stress Scale-10 to guide the design and power calculations for a future trial testing efficacy [69,70]. We will compute the effect sizes of change in these scores to cautiously guide future work. Proof of concept will be demonstrated if the decrease in caregiver stress (Perceived Stress Scale-10, the primary outcome in future trials) in the intervention group from baseline to posttest is greater than in the WA group, with at least small to moderate effect sizes favoring HMP (between-group test of superiority).

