## Methods

### Study Design and Setting

This NIH stage 1B, single-blind, feasibility, proof-of-concept RCT is testing HMP versus WA (time- and dose-matched control) in caregivers of persons with ADRD. Data collection is underway (started in February 2023; n=27 caregivers as of June 2023). We plan to recruit 80 caregivers of persons with ADRD reporting elevated levels of stress. Our institutional review board approved this study (2022P001601). Figure 1 provides an overview of the study design and timeline.

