**Inclusion**			
	Age 18 years or older	Most caregivers are adults; study procedures are formulated for adults only	
	English fluency and literacy	Measures, instructions, and app are in English	
	Meeting criteria for being a caregiver (ie, family or friend of a care recipient who provides care not through an agency) [2]	Population	
	Perceived Stress Scale (4 items) version ≥6 [45]	Population; ensure that the intervention is needed (not all caregivers experience caregiver stress)	
	Willing to be randomized	Necessary for scientific rigor	
	Care recipient must be rated >1 on the Functional Assessment Staging Tool [46]	Population; ensure that caregivers have a threshold of caregiving tasks	

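### The PSS-10 contrast is defined as a difference in change from baseline with no baseline adjustment stated; an adjusted contrast would be more precise at almost no cost

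*Protocol article*

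**What the plan says.** All of this is in the protocol article.

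- **Contrast** (Data Analysis): "we will estimate between-group differences in changes from baseline to posttest (12 weeks) to follow-up (20 weeks) as proof of concept". The same section says that effect sizes of change will be computed.
- **Proof-of-concept rule** (Data Analysis): it is met if the fall in stress "in the intervention group from baseline to posttest is greater than in the WA group". The rule also sets a minimum magnitude, but only in words: "with at least small to moderate effect sizes favoring HMP (between-group test of superiority". No number is attached to small to moderate.
- **Model** (Data Analysis): "We will use variance estimates from repeated-measures analysis of data on Perceived Stress Scale-10 to guide the design and power calculations". The terms of that model, including how baseline enters, are not given. Variance components are to be estimated for each outcome.
- **Purpose** (Data Analysis): "our analysis will not assess efficacy, as we are not powered to do so".
- **Randomization** (Enrollment): it follows completion of the baseline surveys. "Our senior biostatistician programmed randomization into REDCap and stratified by gender".
- **Sample** (Study Design and Setting): "We plan to recruit 80 caregivers of persons with ADRD reporting elevated levels of stress". Entry requires "Perceived Stress Scale (4 items) version ≥6" (Table 1). The dropout benchmark in Table 2 allows up to 30% attrition.

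**The concern.** The article puts the PSS-10 comparison on the change scale three times: in the contrast, in the effect sizes and in the proof-of-concept rule. A plain change score fixes the slope of posttest on baseline at 1. When the actual slope is lower, part of the baseline noise is carried into the treatment contrast. Baseline PSS-10 is collected on everyone before randomization, so conditioning on it is open to the trial at no cost.

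Naming a repeated-measures analysis does not settle the matter. With complete data, a model that treats baseline as one of the responses and leaves the arm means free at every visit gives exactly the change-score contrast. The gain comes only if baseline is a covariate or the baseline means are constrained equal, and the article states neither.

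At stake is the precision of the estimate behind the proof-of-concept decision. That decision turns on the size of an effect, so it is directly exposed to noise in the estimate.

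**Working it through.** **Inputs from the article.** Total 80; 27 enrolled so far (14 HMP, 13 WA), of whom 24 are women and 3 men; attrition benchmark 30%, so 80 × 0.7 = 56 completers.

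**Assumptions, because the article gives no value.** 1:1 allocation (n = 40 per arm, or 28 after attrition); equal SDs at baseline and posttest, set to 1; baseline–posttest correlation r from 0.3 to 0.8; a proof-of-concept threshold of 0.3 SD; a gender difference g of 0.2 to 0.5 SD.

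**The article's own figure.** The 80 comes with no alpha, power, effect size or SD, so there is nothing to reproduce, and efficacy power is disclaimed.

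**Formulas.**
- Change score: Var = 2(1 − r) × 2/n
- Baseline-adjusted: Var = (1 − r²) × 2/n
- Ratio, adjusted to change: (1 − r²) / [2(1 − r)] = (1 + r)/2

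**At r = 0.5, n = 40.**
- Change: 2 × 0.5 × 2/40 = 0.0500, SE 0.224, half-width 1.96 × 0.224 = 0.44 SD
- Adjusted: 0.75 × 2/40 = 0.0375, SE 0.194, half-width 0.38 SD

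**Across the range.** The adjusted half-widths below include a small-sample factor √(1 + 1/(N − 4)) for estimating the slope. The last column is 80 × 2/(1 + r), the number of change-score participants that would carry the same information as 80 adjusted ones.

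| r | Variance ratio | 95% half-width in SD, 40 per arm: change → adjusted | 28 per arm: change → adjusted | Equivalent N |
|---|---|---|---|---|
| 0.3 | 0.65 | 0.519 → 0.421 | 0.620 → 0.504 | 123 |
| 0.5 | 0.75 | 0.438 → 0.382 | 0.524 → 0.458 | 107 |
| 0.7 | 0.85 | 0.339 → 0.315 | 0.406 → 0.378 | 94 |
| 0.8 | 0.90 | 0.277 → 0.265 | 0.331 → 0.317 | 89 |

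A simulation of 6,000 trials of 80 participants at r = 0.5 gave SEs of 0.220 (change) and 0.192 (adjusted), and 0.192 again when a gender term with no effect on outcome was added.

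**Without equal SDs.** Per-person change variance minus adjusted variance is SD₀² + SD₁² − 2r·SD₀·SD₁ − SD₁²(1 − r²) = (SD₀ − r·SD₁)², where 0 is baseline and 1 is posttest. This is never negative, so the direction does not depend on equal SDs, although the ratio (1 + r)/2 does.

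**Effect on the decision rule (illustration).** Take no true effect, a threshold of 0.3 SD, r = 0.5, and look only at the magnitude part of the rule. The chance that the estimate exceeds 0.3 is P(Z > 0.3/SE):
- 40 per arm: 0.3/0.224 gives about 9% (change); 0.3/0.194 gives about 6% (adjusted)
- 28 per arm: 0.3/0.267 gives about 13%; 0.3/0.234 gives about 10%

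**Gender.** With p = 24/27, p(1 − p) = 0.0988 and R² = 0.0988g² / (1 + 0.0988g²). This is 0.4%, 0.9% and 2.4% for g = 0.2, 0.3 and 0.5.

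**The case against.** **The analysis may well be adjusted.** This is a condensed article, its SAP is not shown, and covariate lists are commonly left there. A difference in change is also compatible with adjustment: regressing change on arm and baseline gives the same arm effect as regressing posttest on arm and baseline, and a model with constrained baseline means also reports a difference in change. This stands. A reader might infer that the protocol prescribes an unadjusted analysis; it does not say so. What remains is that the article fixes the contrast and the decision rule in change-score terms, and an analysis that follows it literally loses precision.

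**Stage 2 sample size.** A reader might infer that the next trial will be oversized by 2/(1 + r). That would follow only if it were planned on change-score variance. The article plans variance components from a repeated-measures analysis, and these can supply the correlation needed to size an adjusted analysis.

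**Chance imbalance and selection.** A reader might also see a separate harm in chance baseline imbalance at 40 per arm, or in regression to the mean after selection on PSS-4. Under randomization the change contrast is unbiased, and the imbalance is the same variance counted again. The effect of selection cannot be computed from the article, and a narrower baseline range can shrink the loss. For example, with slope 0.5, residual variance 0.75 and baseline variance cut from 1.0 to 0.7 (all assumed), the ratio is 0.75 / (0.75 + 0.25 × 0.7) = 0.81 instead of 0.75.

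**Small stakes.** The primary outcomes are feasibility benchmarks, efficacy is disclaimed, and at r = 0.8 the variance saving is only 10%. All true, and this limits the weight of the point. It does not remove it, because the proof-of-concept rule still depends on the PSS-10 effect size.

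**Conclusion.** The point holds as a low-cost improvement in precision; it is not an error or a bias. The article defines the PSS-10 contrast and the proof-of-concept rule on change from baseline and states no baseline adjustment. If analysed as a plain change score, the estimate has a variance 1/0.90 to 1/0.65 times that of an adjusted one, about 1.1 to 1.5 times, for r from 0.8 to 0.3. The size rests on an assumed r and on equal SDs; the direction does not need equal SDs, apart from the small cost of estimating the slope.

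Gender is a matter of reflecting the stratified design. At the present split of 24 women to 3 men it could explain only about 0.4% to 2.4% of variance, so its omission cannot be called a meaningful loss of precision. Nothing here shows that the sample size of 80 is wrong.

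**What to change.** In Data Analysis, and in the SAP, state that the arm difference in PSS-10 and in each secondary scale at weeks 12 and 20 will be estimated from a repeated-measures model with the baseline score as a covariate, or with baseline means constrained equal across arms. Include gender as the stratification factor. Apply the proof-of-concept effect-size rule to that adjusted estimate, and state which SD standardizes it (the pooled baseline SD would serve). The rule can still be worded as a greater decrease, since adjusted posttest and adjusted change give the same arm difference.

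Report the residual variance and the baseline–posttest correlation alongside the variance components already planned, so that stage 2 can be sized for an adjusted analysis.

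The cost is a change of wording and one or two degrees of freedom. All the variables are already collected.
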